## 3. SUMMARY

Over the past few years we have conducted a series of studies that have provided new, clear evidence for the presence of hypovolaemia in severe malaria. These were the subject of investigation in a previous proposal: ‘The role of hypovolaemia in the acidosis of severe malaria in children’ (SCC no 603). We demonstrated that volume expansion with either normal saline or 4.5% human serum albumin corrected the haemodynamic abnormalities and was associated with improved organ function and reduction in acidosis. In a formal randomised controlled trial we showed that volume expansion with albumin was associated with a significantly lower mortality in children with severe malaria acidosis, especially those admitted in coma. As human albumin solution is costly and not available in Africa in this current study we aim to examine the safety and dose required (efficacy) for the correction of hypovolaemia of a lower cost colloid, Gelofusin in children with severe falciparum malaria complicated by acidosis. This will be compared to a ‘control’ group of children receiving albumin. In this prospective study we aim to enrol 80 children and randomised them to either Gelofusin or albumin. The primary endpoints will be to compare the safety and efficacy of both colloids on the resolution of haemodynamic markers of shock. Secondary end points will be adverse events, including alterations in coagulation homeostasis. The results of this study will form the basis for the future design of multicentre trials comparing colloidal solutions with saline or maintenance alone, which are required before specific treatment recommendations can be made.

## 4. BACKGROUND

In severe malaria, acidosis has been shown to be the best independent predictor of death1. Acidosis in most critically ill children, regardless of the underlying causative disease, is most frequently associated with impaired perfusion, and is generally, treated by volume expansion, optimization of tissue and organ perfusion and the provision of adequate glucose to reduce metabolic production of organic acids2. However, in severe malaria, although current recommendations include volume expansion3, there has been concern that some patients are at risk of developing cerebral or pulmonary oedema, which has resulted in most patients receiving maintenance fluids only or modest volume restriction. Both these complications are infrequent in African children with severe malaria3. Similar fears were raised in the past when treating children with septicaemia complicated by severe central nervous system infection. Subsequently, it has been recognised that fluid restriction is detrimental to brain perfusion in this situation4,5. Moreover, recent studies investigating the role of aggressive early fluid resuscitation in paediatric septic shock (defined by acidosis)6 and dengue shock syndrome7 have demonstrated significant improvements on survival. In neither study were there increases in the rate of pulmonary oedema or clinical features of cerebral herniation following fluid resuscitation, lending crucial support to the premise that volume expansion is safe in a number of severe infections, regardless of aetiology.

**Evidence for hypovolaemia in severe malaria**

## During the past few years we have conducted a series of studies that have demonstrated new, clear evidence for the presence of hypovolaemia in severe malaria. These were covered by a previous proposal: ‘The role of hypovolaemia in the acidosis of severe malaria in children’ (SCC no 603). In summary;

## Retrospective review: In this case note review we found that many of the clinical and laboratory features associated with a poor outcome are recognizable consequences of impaired tissue perfusion; including acidosis (base excess <-8 and/or its clinical correlate, deep breathing), hypotension, dehydration and elevated creatinine. Ancillary features, regarded as part of the clinical picture of the sepsis syndrome, including hypoxia, hypoglycaemia and electrolyte disturbances, were also important factors in predicting a fatal outcome. Overall, shock (hypotension or two or more other features) was present in 84% of deaths. Elevated creatinine, biochemical or clinical features of acidosis and delayed capillary refill time (≥3s) were numerically the three major contributors to the shock score of ≥28.

## Pilot studies: We conducted a prospective phase I study examining the safety of volume expansion for children admitted with clinical features of severe malaria (impairedconsciousness or deep breathing) complicated by acidosis (base excess <-8). Patients recruited to the study underwent continuous monitoring of blood pressure, pulse rate, respiratory rate, oxygen saturation and central venous pressure using a multichannel recorder. Fifty-three children were recruited and all had evidence of compensated shock on admission, with tachycardia, tachypnoea and prolonged capillary refill time (≥3s). Mean central venous pressure (CVP) [standard error] at admission was low: 2.9 [0.5] cm water (see Figure); in the group with severe acidosis (base excess<-15) 44% had hypotension (systolic blood pressure < 80 mmHg). Improvements of haemodynamic indices and a reduction in acidosis followed administration of either saline or albumin. By 8 hours the mean CVP had increased to 7.5 [0.5] cm water (F=34.4, P<.001) and was associated with a reduction in mean respiratory rate 49 [2] to 41 [1], F=7.0, P=.009, reduced tachycardia 151 [5] to 141 [3], F=3.4; P=.06 and reduced capillary refill time. No child developed evidence of the life threatening complications of pulmonary oedema and raised intracranial pressure. We concluded that both albumin and saline were safe and that doses of between 20-40mls/kg given over the first hour after admission resulted in a correction of the features of hypovolaemia and resolution of the acidosis9.

Figure: Central Venous Pressure measurement in children with malarial acidosis: correction of hypovolaemia with volume replacement

Central venous pressure (CVP) measures the pressure in the column of blood returning to the heart (preload). In health, this is normally 5-8cm H2O. In sick children higher preloads ~ 8-10cm are often required. In these children with severe malaria complicated by acidosis CVP was low at admission (0 hours) and normalised following 20-40mls/kg intravenous bolus of 0.9% saline or 4.5% albumin (indicated by the diamond).

## Phase II randomised controlled trial:

## Aims: We aimed to test the hypothesis that volume expansion with a colloidal solution would enable the acidosis and hypovolaemia of severely ill children with malaria to be corrected with less risk of precipitating cerebral oedema, than if crystalloid was used. In this trial we chose to use 4.5 % human albumin solution for the colloid and 0.9% saline as the crystalloid10. The use of albumin as a major resuscitation fluid for septic shock is well established in European and Australian paediatric critical care and has been associated with a general reduction in mortality with the least adverse reactions11,12, despite the results of a recent meta-analysis13.

## Design and results: We randomly assigned children with severe malaria and metabolic acidosis (base excess <-8) to treatment with either albumin or saline: patients with moderate acidosis (base excess between –8 and -15) received 20 ml/kg; and those with severe acidosis (base excess <-15) received 40 ml/kg. For ethical reasons, a control (maintenance only) group was only included for patients with moderate acidosis. 150 children were enrolled. There was no difference in the rate of resolution of acidosis between the groups; however, requirement for alternative treatments was significantly more common in the maintenance only control group (P =0.004). Overall, mortality was significantly lower in patients receiving albumin (2/56; 3.6%) than those treated with saline (11/61; 18%) (2= 6.1, P=0.01). The improved mortality was entirely confined to the children admitted in deep coma, where mortality was (1/21; 5%) in albumin recipients as compared with (11/24; 46%) in saline recipients (P =0.002). Only one child developed pulmonary oedema (in the saline group) (overall incidence <1%) and 10 (7%) of the 135 survivors had neurological sequelae. Prior to the study mortality in children with malaria and severe acidosis had been consistently documented at between 25-40%, hence the low rate in the albumin recipients (4%) is lower than any previously reported patients with similar severity of disease. Our finding that the beneficial effect of albumin was greatest in the comatose patients (5% in the albumin treated group) and that most of the deaths in the saline treated patients appeared to be neurological in origin, is consistent with the predicted physiological effects of albumin14.

## Interpretation of the findings

Treatments aimed at correcting volume deficits and improving tissue perfusion carry the risk of increasing cerebral oedema. Non-colloidal containing solutions such as normal saline are freely distributed across the extracellular compartment and will move rapidly from the intravascular compartment into the tissues with the potential risk of accentuating RICP and causing pulmonary oedema. This risk is greatly increased by the presence of hypo-albuminaemia. Children with severe malaria frequently have hypo-albuminaemia, a factor we reckoned that would favour the use of colloid replacement10. In this study we demonstrated some support for this principle, since the major difference in mortality between saline and albumin treated children was limited to the high-risk group presenting with respiratory distress and coma. A number of additional questions arise from the findings of this trial.

First, maintenance only fluid was only given to the lower mortality group with moderate acidosis, in the absence of a control group receiving maintenance fluids alone in those with severe acidosis, where most deaths occurred, it is not clear whether saline administration is simply inferior to albumin, but preferable to fluid restriction, or whether saline administration is actually hazardous. Second, since saline is the standard resuscitation fluid in use across Africa, and albumin is expensive and currently unavailable in most African centres, further work is required before definitive treatment recommendations can be made. Finally, now we demonstrated the principal that volume resuscitation with albumin maybe superior to saline in those with coma the safety profile of alternative cheaper colloid should be examined. In this proposal we aim to examine the safety and efficacy of the gelatin-based colloids in the treatment of acidosis of severe malaria.

## Choice of colloids

There are 4 general types of colloid products available for clinical use; albumin, dextrans, starches and gelatins15. They differ in their molecular weight, colloid osmotic pressure and duration within the intravascular compartment. Albumin, prepared from pooled human donors, has the best safety profile but is in short supply and is therefore expensive.

**Dextrans**: Dextrans (Dextran 40 and Dextran 70) are glucose polymers that initially produce intravascular volume expansion by increasing osmotic load, but their effect is transient. Smaller polymers (Dextran 40) rapidly escape from the intravascular compartment; 50% of the dextran polymer is lost within 3 hours, whilst the larger polymers within Dextran 70 escape less rapidly (35% clearance within 12 hours)16. The main route of excretion is renal, some of the extravascated dextran remains in the

Table one: a summary of the characteristics and properties of the colloids commonly used in critical care.

|  |  | Dextrans | | Starches | | Gelatins |
| --- | --- | --- | --- | --- | --- | --- |
|  | **Albumin** | **Dextran 40** | **Dextran 70** | **Hetastarch (6%)** | **Pentastarch** | **Gelofusin** |
| Molecular weight (KD) | 70 | 40 | 70 | 450 | 260 | 30 |
| Plasma volume expansion (ml/500ml infused) | 500 | 500-1000 | 500-700 | 500-700 | 600-800 | 500 |
| Cost (US $) per litre (in USA) | 360 | 200 | 150 | 130 | 150 | 15-20* |
| Incidence of allergic reactions | 0.011 | 1.1 | 1.1 | 0.09 | Not available | 0.06 |
| Effect on clotting | v. mild, dilutional | Decreases in von Willebrands factor |  | Increase in prothrombin and partial thromoboplastin times |  | v. mild, dilutional |
| Comment |  | Decreases blood viscosity | Increases blood viscosity | Prolongs bleeding time |  |  |

* not available USA, UK equivalent price given

extravascular space and exert an osmotic effect. Another major feature of the dextrans is that they lower blood viscosity and thus are favoured for use during surgery, as they decrease the risk of deep vein thrombosis and pulmonary embolus17. Dextran administration is associated with a coagualopathy (decreased fibin clot formation), decreased levels of von Willebrand factor (vWF) and associated factor VIII:c activity. The decrease in wVF and VIII:c are greater than expected by dilution. VWF is the ligand between the platelets surface and the endothelial wall and this has resulted in prolonged bleeding times in vivo18. The rate of allergic reaction is 1.1%.

**Starches:** Hetastarch (hydroxyethyl starch, HES) is produced by partial hydrolysis of amylopectin, which is made more soluble by the addition of glucose molecules. The 6% solution is the most commonly used solution (Hepaspan) and closely resembles 5% albumin; both are isotonic and increase the intravascular volume by the amount infused. The half life of hetastarch is longer (24 –36hours) than albumin15. It is both excreted by the kidneys and degraded by the enzymatic action of amylase. The major set back is that it alters haemostasis leading to increases in prothrombin time, partial thromboplastin time and bleeding time, and decreased levels of VIII:C and VIII:Ag18. As a result, the maximum daily dose recommended for adults is 1500mls/day and for children is 20mls/kg15. Pentastarch has a greater osmotic pressure and thus leads to greater volume expansion, nearly twice that of the volume infused. However, the half life is only 2.5 hours; 60% is excreted in the urine. Furthermore, Pentastarch is associated with similar haemostatic problems as Hetastarch. Allergic reactions are rare; < 0.1%.

**Gelatins:** The gelatins are produced from alkali-treated bovine collagen, which hydrolyses the esters and peptide links, followed by suspension in aqueous solution. There are two types of gelatins the succinylated gelatins (Gelofusin) or urea-linked gelatins (Haemacell). Both types of solutions are polydisperse. The small particles exert a large osmotic effect, but are then rapidly lost by glomerular filtration15,17. The volume expanding effect last for ~4 hours17. Compared to human albumin, the modified gelatins have similar shown efficacy in formal randomised trials19. Reports of haemostatic abnormalities after infusion of gelatins are rare and in vitro changes are related to dilution rather than a direct effect on the clotting cascade18. Allergic reactions are also rare < 0.1%. Haemacell has a higher calcium (6.26mmol/L) (which may lead to clotting if infused with blood) and higher potassium (5.1mmol/L) than Gelofusin15. Thus, the modified gelatins, in particular Gelofusin, emerge as the colloid with, theoretically, the least anticipated complication rate and for this study will be considered in this current study as the colloid of choice.

**Theoretical considerations for the use of colloid in severe malaria**

Most of in-vivo trials examining the effect of different colloids on haemostasis (usually measure by blood loss) have been conducted in clinically stable patient groups undergoing corrective orthopaedic or cardiac surgery. In septic shock coagulation and haemostasis is disordered. In severe malaria bleeding secondary to disseminated intravasular coagulation (DIC)3 and procoagulant activity has been reported in adults with severe malaria20,21. In children whilst DIC is rarely encountered, little to no information exists on the abnormalities in coagulation and homeostasis22. There are however, a number of considerations when considering the use of non-albumin colloids. Firstly, in severe malaria moderate degree of thrombocytopenia is invariable22. In children admitted with severe malaria to KDH, thrombocytopenia (platelets counts < 150x1012) is common (>55%)23. Dextrans and starches are known to reduce von Willebrand factor and increase the risk of bleeding18. In the presence of thrombocytopenia, a von Willebrand-like syndrome is a possible complication. Albumin has no effect on coagulation and the effects by gelatins are mild, usually related to a dilutional effect18.

**5. JUSTIFICATION**

We have previously showed that rapid volume expansion with 4.5% albumin shortly after admission is safe and has lead to a significantly lower mortality in children with severe malaria acidosis, especially those admitted in coma. As human albumin solution is costly (£45 per 500mls in the UK ~KSH 5,850) and not easily available in Africa we aim to examine the safety of a lower cost licensed colloid, Gelofusin (£5 per 500mls ~KSH 650) when used to correct hypovolaemia. The safety and dose response will be compared to that of albumin. Since most non-albumin colloids have some effect upon coagulation, part of this trial will include serial measures of coagulation activation[[1]](#footnote-2).

**6. NULL HYPOTHESES.**

1. There is no difference in the safety profile or effect on physiological parameters of shock using gelatin-based colloids and albumin for the correction hypovolaemia in children with severe malaria.
2. The use of either of the two colloids will lead to no changes in coagulation after administration.

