### Secondary aims

1. To establish whether volume correction by Gelofusin can be undertaken safely and is comparable to albumin.
2. To examine whether the volume of Gelofusin required for correction of the physiological parameters of hypovolaemic shock is similar to albumin.
3. To establish whether albumin or Gelofusin lead to derangements of coagulation.

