##### c. Sampling

1. **Sample size determination**

These are pilot studies designed primarily to examine the safety of Gelofusin in children with severe malaria complicated by acidosis. As Phase I studies they are designed to provide adequate data to justify progression to next phase ie: multicentre studies, but with the desire to avoid exposure of a large group of children to a therapeutic intervention for which there is no available data in severe malaria. The trial will therefore, provide important data on the volumes required of Gelofusin in achieving satisfactory improvements in haemodynamic features of shock such in a similar manner to that which has been previously observed in children given albumin9. Formal sample sizes will therefore not be calculated. We aim to recruit 80 children: 40 will have moderate acidosis and 40 will have severe acidosis. 20 children in each group will receive Gelofusin and 20 will receive albumin. Since we showed that the greatest benefit of albumin was in those with coma24, at least 50% of the children recruited will have coma. Gelofusin, would be used in preference to albumin in larger studies if mortality were 10% (confidence interval 7.5-12.5%) or less.

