**b) Provisions for data verification and validation.**

Currently all data is directly entered in File-Maker Pro where most variables entered have dichotomous values only and the values for numerical fields are selected from a list. Initial and final diagnoses are also chosen from a list of common diagnoses. The programmes have been written to include logical and range checks and flags for the reduction of duplication errors. Appropriate information quality control procedures are already established. Children fulfilling the admission criteria for the study will be flagged by the computer to alert the admitting physician.

Descriptive statistics will be used to compare the clinical characteristics of the groups at baseline (admission), 30minutes, 1 hr, 4 hrs, 8 hrs, 12 hrs and at 24 hours, by intervention. The major outcomes of interest will be the resolution of clinical features of shock and major side effects or complications; development of abnormal clotting indices, pulmonary oedema and death (as dependant variables) between the different interventions (independent variables). The primary measure of this outcome will compare the proportions attaining level one goals for resuscitation in those receiving albumin and Gelofusin. Using ANOVA baseline (admission) haemodynamic parameters (heart rate, respiratory rate, oxygen saturation, mean blood pressure and coma score) will compared to those at 1 hr, 2 hours and 8 hours between the different intervention groups. For the purpose of analysis percentage mean change in the parameter will be used between the baseline and next time point.

Expected outcome: We have shown that albumin results in low mortality (< 5%), whilst saline was associated with an overall mortality ~20%, rising to 46% in those with coma. Historical control data from children with the same clinical criteria show mortality was between 30-50%, when volume expansion was not routine. If the dose response to Gelofusin is similar to albumin then assessment of the clinical safety of Gelofusin will take the above mortality data into consideration, as well as the evidence arising from the coagulation studies.

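### Hypothesis 1 is a null of no difference, so its test cannot establish the comparability and similarity that secondary aims 1 and 2 and section 9(b) ask about

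*Protocol*

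**What the plan says.** **Hypothesis.** Section 6 of the protocol states hypothesis 1 as a null of sameness: "There is no difference in the safety profile or effect on physiological parameters of shock using gelatin-based colloids and albumin".

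**Aims.** The first secondary aim in section 7 is "To establish whether volume correction by Gelofusin can be undertaken safely and is comparable to albumin". The second is "To examine whether the volume of Gelofusin required for correction of the physiological parameters of hypovolaemic shock is similar to albumin". The primary aim is different in kind: it asks whether Gelofusin can safely correct volume depletion and acidosis, with no reference to albumin.

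**Analysis.** Section 9(b) names as the primary measure a comparison between the arms of the proportions reaching level one goals. It adds ANOVA on haemodynamic change from baseline. Its paragraph on the expected outcome then sets a condition: "If the dose response to Gelofusin is similar to albumin then assessment of the clinical safety of Gelofusin" will draw on earlier mortality data and on the coagulation evidence. The protocol gives no margin, interval criterion or definition for either *comparable* or *similar*.

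**Size.** Section 8(c), on sample size, calls these pilot, Phase I studies and says "Formal sample sizes will therefore not be calculated". It plans as follows: "We aim to recruit 80 children: 40 will have moderate acidosis and 40 will have severe acidosis", and "20 children in each group will receive Gelofusin and 20 will receive albumin". The same section gives the only stated rule for preferring Gelofusin in larger studies, which is a mortality threshold of 10% or less.

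**The concern.** The hypothesis and the questions point in opposite directions. A test against a null of no difference can give evidence that the colloids differ. When it does not reject, it leaves open both that they are alike and that the trial was too small to tell them apart. Secondary aims 1 and 2 and the condition in section 9(b) need an answer of the first kind.

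With no other criterion stated, non-rejection of hypothesis 1 is the only formal route the protocol offers to the words *comparable* and *similar*. A weaker comparison makes non-rejection more likely, so the words would be easiest to apply where the evidence is thinnest. A real shortfall of Gelofusin in correcting shock could then be reported as comparability, and could satisfy the section 9(b) condition.

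**Working it through.** **Inputs from the protocol.** Two acidosis groups × (20 Gelofusin + 20 albumin) = 80 children, which reproduces the stated total and gives 40 per arm. The 80 has no power or precision basis to reproduce, as section 8(c) says.

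**Assumptions.** The protocol states no significance level, expected attainment rate or margin. I take two-sided 0.05 and attainment of level one goals between 50% and 90%. Section 9(b) names no test for the proportions, so chi-square and Fisher are both shown.

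**1. What the trial can exclude if the arms are truly equal.** The 95% CI half-width is 1.96 × √(2p(1−p)/40).

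| Attainment p, both arms | Calculation | Half-width |
|---|---|---|
| 50% | 1.96 × √(0.50/40) | 21.9 points |
| 70% | 1.96 × √(0.42/40) | 20.1 points |
| 80% | 1.96 × √(0.32/40) | 17.5 points |
| 90% | 1.96 × √(0.18/40) | 13.1 points |

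Within one acidosis group (20 per arm) the same formula gives 31.0 points at 50% and 18.6 at 90%.

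**2. How often a real deficit would go undetected.** The normal approximation to chi-square power is Φ{[d − 1.96√(2p̄(1−p̄)/40)] / √[(p₁(1−p₁) + p₂(1−p₂))/40]}.

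- 80% against 60%: d = 0.20 and p̄ = 0.70, so (0.200 − 0.2008)/0.100 = −0.008 and power is 0.497. Exact enumeration with Fisher's test gives 0.408.
- 80% against 70%: d = 0.10 and p̄ = 0.75, so (0.100 − 0.1898)/0.0962 = −0.93 and power is 0.175 (0.177 by enumeration of the chi-square test). Fisher gives 0.123.

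A true 20-point deficit of this kind would therefore give a non-significant result in about 50% to 59% of trials, and a true 10-point deficit in about 82% to 88%.

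**3. Volume, for secondary aim 2.** No standard deviation is given, so this is in SD units. The 95% CI half-width is 1.96 × √(2/40) = 0.44 SD. The difference detectable with 80% power is (1.96 + 0.84) × √(2/40) = 0.63 SD.

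**4. What a margin would demand.** With margin m, one-sided 0.025, 80% power and equal true rates, n per arm = 2p(1−p)(1.96 + 0.84)²/m².

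- At p = 80%: 252 per arm for m = 10 points and 63 for m = 20 points.
- At p = 90%: 142 per arm for m = 10 points and 36 for m = 20 points.

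With 40 per arm, power to exclude a 20-point deficit is Φ(0.20/SE − 1.96), where SE = √(2p(1−p)/40). This gives 43% at p = 50%, 61% at 80% and 85% at 90%. These margins are illustrations only.

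**The case against.** The strongest reply is that the protocol claims less than its hypothesis might suggest. Four points deserve weight.

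- **The aims are open questions.** They ask *whether* Gelofusin is comparable or similar. A reader might infer that the trial will declare comparability on a non-significant test, but no sentence says so. This stands: the risk is one of interpretation.
- **Progression rests elsewhere.** A reader might infer that failure to reject opens the way to larger trials. The text does not support that. The stated rule for larger studies is the Gelofusin mortality threshold in section 8(c), which is not a comparison with the albumin arm. The section 9(b) condition leads to a safety assessment and is tied to no p-value.
- **It is a pilot.** That is a fair reason for having no power calculation, and the summary leaves treatment recommendations to later multicentre trials. It does not make non-rejection evidence of similarity.
- **A statistical analysis plan may set out intervals or a margin.** It may, and the absence of a CI plan is not the criticism here. The null and the aims are worded in the protocol, and the mismatch between them has to be resolved there.

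It would also be too strong to say that 40 per arm can never exclude a deficit well below 20 points. If both arms attain 90%, the half-width is about 13 points.

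**Conclusion.** The point holds as a mismatch between hypothesis 1 and the questions in secondary aims 1 and 2 and the section 9(b) condition. It does not reach the primary aim or the mortality rule for larger studies. It should be corrected, but it does not undermine the trial as a whole.

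The size depends on assumed attainment rates. Across 50% to 90% in both arms, the interval for the difference extends about 22 to 13 points either side. If the true rates were 80% and 60%, the planned comparison would detect the deficit no more than about half the time. At that precision a non-significant result is compatible with a substantial shortfall and cannot by itself justify either word.

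**What to change.** 1. Restate hypothesis 1 (section 6) and secondary aims 1 and 2 (section 7) as estimation: report the Gelofusin minus albumin difference with its 95% CI for level one goal attainment, volume of colloid and mortality.
2. State that a non-significant test will not be described as comparable or similar.
3. In the secondary aims and in the section 9(b) condition, reserve those words for a CI that excludes a deficit fixed, with reasons, before the data are seen.

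The change needs no extra children, measurements or visits. Its cost is that the trial's claims become more modest: with 40 per arm, even a 20-point deficit would be excluded with good probability only if attainment is near 90% in both arms, so the trial may end without being able to use either word.
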